### Statistical analysis

Patients with COPD in the intervention and control areas will first be described using parameters of point estimation and their 95% confidence intervals. The groups will then be compared based on bivariate hypotheses on pre- to post-intervention changes in process and outcome variables. The statistical tests that will be used will depend on the nature of the variable studied.

Analysis of the health-care dimension will focus on the impact of the COPD PROCESS model within the health-care delivery system (objective 1), based on comparing the utilization of resources and visits to primary and specialist care facilities in the intervention and control areas. The principal outcome measure will be the change in annual rate of scheduled and unscheduled admissions that are made with a main diagnostic code of COPD (Table 1) or another code related to a respiratory system process. The year prior to implementation of the PROCESS management system will be compared to the last 12 months of implementation. The difference between the rates of the two study areas will be estimated using the indirect standardization method in which the population assigned to each health-care area will be used as the standard. If possible, a more precise analysis of the differences in rates will be undertaken by constructing linear multiple regression models adjusted for the distribution of the dependent variable (negative binomial, Poisson, beta), a procedure which corrects for confounding factors.

For the clinical dimension, health status and quality of life will be compared between patients in the intervention and control areas (objective 2). The main outcome measure will be minimal clinically significant differences between pre- and post-intervention quality-of-life scores. A test of comparison between two independent means will be used for comparisons with the control group. If multivariate analysis is necessary, multiple regression models will be constructed.

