The magnitude and seriousness of the problem contrast with the fact that COPD is a preventable, treatable and modifiable disease. COPD begins to develop earlier than is usually assumed and recognition generally comes when the disease is already in advanced stages. The rate of underdiagnosis is alarming. One population-based study found that 78.2% of cases identified had not been previously diagnosed [2]. The reasons for this are not well understood, but many agree that inadequate coordination between primary and specialized care may play an important role [10]. Health-care systems have long been characterized by a lack of cohesion between these two levels, and even today, no optimal model has emerged to bridge the gap. Spanish outpatient care has been reformed in recent years, leading to substantial primary health-care improvements in the public sector. However, the nature of relations between primary care physicians and specialists has not been a central concern, contributing to the gap between the two levels of care and to mutual lack of understanding. This is of particular importance with regard to COPD given its high prevalence and wide range of severity in the patient population. The first attempts at writing agreements on care for COPD patients were undertaken by scientific societies only a few years ago [11], but clear protocols to guide relations between levels of care, validated to demonstrate their effectiveness and efficiency, are still lacking. Nor are there studies on which to base the recommendation of one protocol over another.

A model for managing the care of COPD patients is still needed. The aim of such a model would be to integrate available health-care resources, helping the various clinicians involved to agree on a common approach and act in concert. An ideal, shared model would facilitate cooperation among health-care staff on the basis of well-defined responsibilities, agreement on working protocols and mutual exchange of information. It would serve to promote effective health-care for all patients as well as the efficient use of resources.

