## Methods/Design

A quasi-experimental design based on comparison of two non-randomized groups was chosen to assess the effectiveness of the multidisciplinary, multicenter COPD PROCESS management model. The intervention group will consist of all patients with COPD in the area served by Hospital de la Santa Creu i Sant Pau in Barcelona. The control group will comprise all COPD patients in the area served by Hospital de la Vall d'Hebron, also in Barcelona. Randomization was not feasible because only health-care professionals within the intervention area can undertake the coordinated care protocols necessary for implementing the PROCESS protocol. The study will include pre- and post-intervention assessment after 18 months (Figure 1). This project and the study were presented to and approved by the Clinical Research Ethics Committee of Hospital de la Santa Creu i Sant Pau.

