Exacerbations in the last year:^†‡^	Defined as the worsening of respiratory symptoms requiring treatment with antibiotics or oral corticosteroids or both (moderate exacerbation) or hospitalization (severe exacerbation) or a combination of the two degrees of severity (based on [45])
Complications and potential complications:^‡^	Primary care nursing diagnosis (according to the Catalan Health Institute's adaptation of the North American Nursing Diagnosis Association (NANDA), February 2003).
Health care in the past year:^†‡^	Primary care clinic visits for any reason (including the general practitioner, the nurse or the respiratory medicine specialist); number of home visits made in the past year; number of visits to hospital (outpatient, emergency, admissions).
Quality of life:^‡^	Respiratory-disease related quality of life (Chronic Respiratory Questionnaire [46])
Systemic inflammatory status:^‡^	C-reactive protein (capillary blood levels: QuikRead^® ^CRP 101. Orion Diagnostica, Espoo, Finland)
Other:^†‡^	Exitus

^† ^Measures evaluating the health-care dimension of the COPD PROCESS model. Information will be gathered on the population of patients with chronic obstructive pulmonary disease in each of the two study areas (clinical and administrative data from the databases of the participating centers).

^‡ ^Measures to evaluate the clinical dimension of the COPD PROCESS model. Information will be gathered on patients in the intervention and control cohorts by consulting patient medical records and arranging for patient visits in each of the centers.

All measurements will be recorded at the start of the study and after 18 months' experience implementing the management program.

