### Data collection and analysis

Figure 1 shows details of analysis of the pre- and post-intervention data.

The clinical and administrative information systems at the primary care centers are computerized (eCAP in the ICS centers and other applications such as the OMI-AP or SinAPsis in other centers). Primary care physicians in the intervention area will also be using PROCESS software linked to these applications. That software will serve two functions: it will guide decisions to bring them into line with the PROCESS recommendations and will also provide a place to record the actions taken. The participating hospitals also have computerized clinical and administrative information systems for outpatient, emergency, and day-hospital activity as well as admissions. The data will be merged into a single COPD patient registry for each of the areas (intervention and control). Patients will be identified by their personal identification code. Information in this registry will, if possible, be complemented with information from records of prescriptions for outpatient respiratory therapy, from the Minimum Basic Data Set for discharged patients, from records of pharmaceutical prescriptions filled, and from the death registry of the Department of Health of the Government of Catalonia (Generalitat). Finally, data will also be available from the records of an allied social-welfare and health-services program (Centre Palau).

The clinical data of each patient in each cohort will be collected by two nurses experienced with COPD management who will go to the primary care center of each patient. There they will systematically extract information from the medical records (medical history and other documents in digital form or on paper). They will interview each patient to check the inclusion criteria, obtain informed consent, ask questions relevant to the outcome measures, perform lung function tests, and administer a questionnaire about health-related quality of life.

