### Strengths and possible limitations of the study

The limitations inherent to any evaluative or quasi-experimental study are also present in this research. Patients cannot be randomized for this study. Nonetheless, the design is the most robust one available and will provide the strongest evidence possible, within the existing constraints. Possible differences that might emerge between the control and intervention groups will be adjusted by applying multiple regression analysis.

The use of clinical and administrative databases as sources of information places limitations on the comprehensiveness of the analysis and its validity, as the quality of data is dependent on the information storage interface and its adequate and proper use by health-care professionals. It was expressly decided, however, not to create dedicated databases given that the pragmatic nature of the model requires that the information sources be integrated into the daily work routines of the physicians and nurses who are caring for the patients. The inclusion of the study cohorts will counterbalance this limitation.

Implementing a multidisciplinary model over such an extensive geographic area and working with such a large number of clinical caregivers is a complex undertaking. Adequate and consistent adherence to the PROCESS protocols at all the health-care facilities will require a very high level of dedication. Therefore, it will be essential to integrate the project-specific software into the records of the care facilities. Periodic meetings to coordinate and supervise the participants will also be required.

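### With one year before and one year after in two areas, a differing admission trend cannot be separated from the programme effect; earlier rates should be shown and the conclusion limited accordingly

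*Protocol article*

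**What the plan says.** The Methods/Design section states that "A quasi-experimental design based on comparison of two non-randomized groups was chosen", with one hospital area as intervention and one as control. Under Statistical analysis, "The principal outcome measure will be the change in annual rate of scheduled and unscheduled admissions" with a main diagnosis of COPD or another respiratory code, and the windows are fixed: "The year prior to implementation of the PROCESS management system will be compared to the last 12 months of implementation". Study variables confirms two measurement times: "All measurements will be recorded at the start of the study and after 18 months' experience implementing the management program".

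The area rates are compared by indirect standardization. Where feasible, count-type regression is added, described as "a procedure which corrects for confounding factors". No earlier period, trend term or check of parallel trends is named. The Strengths and limitations section answers the lack of randomization with multiple regression and says that "the design is the most robust one available and will provide the strongest evidence possible, within the existing constraints".

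Three other places bear on the point:
- **Setting:** the intervention area has 10 ICS centres and 7 run by other kinds of provider; all 17 control centres belong to the ICS.
- **The COPD management model:** preparatory actions began in 2006, are due to finish at the end of 2008, and do not take place in the control area.
- **Data collection and analysis:** "The participating hospitals also have computerized clinical and administrative information systems for outpatient, emergency, and day-hospital activity as well as admissions".

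**The concern.** A difference in pre-to-post change between two areas equals the programme effect only if the two admission rates would otherwise have moved in parallel. With a single pre-year this cannot be checked, and no adjustment can be estimated. Standardization and patient covariates account for who the patients are, not for an area's own trajectory.

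The article gives two reasons to doubt parallel movement. The two primary care networks are managed differently, so organizational change may have reached them unequally. In addition, the planned pre-year (about 2008) lies inside a phase of training, information sessions and spirometry work confined to the intervention area. If those actions affected admissions, the areas were already diverging before the baseline.

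A drift already under way in either area would then be reported as success or failure of PROCESS, in one of the two principal endpoints.

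**Working it through.** The article states no effect size, power or trend for admissions, so there is no figure of its own to reproduce. What follows shows the structure and then illustrates the size.

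**1. Identifiability.** Take the log ratio of the intervention rate to the control rate. It needs three parameters: a level, a differential slope and a programme step. The design supplies two values, one pre and one post. The design matrix with rows (1, −0.5, 0) and (1, 1.0, 1), time in years, has rank 2. Slope and step cannot be separated.

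**2. Distance between windows.** Assume full implementation from January 2009, since the preliminary phase ends with 2008. The pre-year is 2008, midpoint 1 July 2008. The last 12 of 18 months run from July 2009 to June 2010, midpoint 1 January 2010. The gap is 1.5 years.

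**3. Spurious change.** For an assumed differential trend g per year and no programme effect, the spurious ratio is (1 − g)^1.5:
- 2%: 0.98^1.5 = 0.970, a 3.0% change
- 3%: 0.97^1.5 = 0.955, a 4.5% change
- 5%: 0.95^1.5 = 0.926, a 7.4% change

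**4. Would it look significant?** Inputs are 32,248 and 32,114 expected patients (Abstract and Setting assign these to opposite areas; they are too close to matter here) and 12.8% hospitalized per year (Background), assuming one admission each. This gives E = 4,128 and 4,111 admissions per year. With dispersion φ, SE(log ratio of rate ratios) = √[φ(2/E₁ + 2/E₂)]. For φ = 1: √(2/4,128 + 2/4,111) = 0.031, a 95% half-width of 1.96 × 0.031 = 0.061.

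The expected counts may be too high, because entry requires a recorded code and the Background cites a study in which 78.2% of cases were undiagnosed. Applying the remaining 21.8% (an assumption) gives about 900 and 896 admissions.

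With b = 1.5 × |ln(1 − g)|, the two-sided 5% rejection rate is Φ(b/SE − 1.96) + Φ(−b/SE − 1.96):

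| Scenario | SE | 2%/yr | 3%/yr | 5%/yr |
|---|---|---|---|---|
| about 4,100 admissions, φ = 1 | 0.031 | 16.3% | 31.1% | 69.5% |
| about 4,100 admissions, φ = 4 | 0.062 | 7.7% | 11.3% | 23.5% |
| about 900 admissions, φ = 1 | 0.067 | 7.4% | 10.5% | 21.1% |
| about 900 admissions, φ = 4 | 0.134 | 5.6% | 6.4% | 8.9% |

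The bias is the same in every row; only the chance of declaring it significant changes.

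**5. What earlier data would buy.** Fit level, differential slope and step to the monthly log rate ratio, with months 0–6 after implementation left out, φ = 1 and no autocorrelation. Using the larger counts, the SE of the slope per year is 0.054 with 12 pre-months, 0.026 with 24, 0.014 with 36 and 0.007 with 60. Monthly counts within the planned pre-year alone are therefore not enough. The SE of the step is 0.087, 0.058, 0.044 and 0.034 respectively, against 0.031 for the planned contrast.

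Those step SEs assume that the pre-months immediately precede implementation. If 36 clean months come instead from 2003–2005 and 2006–2008 is set aside, the slope SE stays at 0.0144, but the slope is carried over 5.5 years between midpoints rather than 2.5. The monthly variance is 12/4,128 + 12/4,111 = 0.00583. The step SE is then √(0.00583/36 + 0.00583/12 + 5.5² × 0.0144²) = 0.083.

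**The case against.** A controlled before-after comparison is a recognised design. The concurrent control in the same city removes fixed differences and any trend that both areas share. The article admits the limits of a quasi-experiment and qualifies its robustness claim by the existing constraints. All of that stands, and the point concerns differing trends only.

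It may also be said that a condensed article leaves trend checks to the full protocol, and that the design figure is not shown. Supplementary checks could sit there. The main contrast and its windows are nevertheless fixed in the text.

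A reader might infer four stronger things that the documents do not support:
- **That the areas are shown to diverge.** The Background remark that "Spanish outpatient care has been reformed in recent years, leading to substantial primary health-care improvements in the public sector" describes a national change, which the control area would absorb if it affected both areas alike. No area-specific trend is reported; the 2–5% per year is assumed.
- **That a drift would be declared significant.** At 5% per year this is likely only under the most favourable precision.
- **That several earlier years are certainly available.** The article says that the hospital systems are computerized, not how far back they go. The discharge data set is only a possible addition. A historical denominator of coded, active patients would also need old primary care registers from several software systems.
- **That an interrupted time series over the preceding three or four years should replace the main analysis.** Most of that period lies in the preparatory phase. A slope fitted there could absorb early programme effect and project it forward, and precision would fall.

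**Conclusion.** The concern holds in limited form. The stated contrast cannot distinguish a differing area trend from the programme effect, and the planned adjustment does not cure this. That part is structural and needs no assumption.

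The size depends on an unknown trend: 3.0%, 4.5% or 7.4% for an assumed 2%, 3% or 5% per year over 18 months. How often 5% per year would yield a false positive runs from about 70% down to 21–24% with either fewer coded patients or overdispersion, and to about 9% with both. These figures rest on the assumed start date, one admission per hospitalized patient and the coded fraction.

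The documents show grounds for doubting parallel trends, not evidence that the trends differ. This is an inexpensive improvement to the plan and does not invalidate the planned comparison.

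**What to change.** Keep the planned contrast and add the following:
1. Extract annual or quarterly respiratory admission rates for both areas from the computerized hospital systems, as far back as records allow and preferably to before 2006. Use one denominator definition throughout, for example all assigned residents, age-sex standardized, which avoids rebuilding old COPD registers.
2. Report the two areas' rates side by side over the whole period.
3. Add a sensitivity analysis by controlled interrupted time series, with 2006–2008 modelled as its own phase rather than as a clean pre-trend.
4. State the parallel-trend assumption. If the trends differ, or the history cannot be obtained, limit the causal conclusion and reword the robustness claim in the Strengths and limitations section.

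The cost is a longer extraction, a check that older coding is consistent, and a clearly wider interval in the sensitivity analysis: a step SE of about 0.044 with 36 adjacent pre-months, or about 0.083 if those months must predate 2006, against 0.031, all before autocorrelation. If the second figure applies, the side-by-side display will be more informative than the adjusted estimate.

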### Setting

The study will be carried out in the patient populations registered with primary care centers within the areas assigned to the respective referral hospitals. The study group will come from 17 primary care centers, of which 10 are managed by the Catalan Health Institute (ICS) and 7 by other types of health-care provider (private for-profit, private nonprofit, and mixed public-private entities). The population base was 322,478 inhabitants over the age of 14 years. The prevalence of COPD in this population was estimated by age and gender from the results of the IBERPOC study [2] and the Catalan Health Survey of 2002 [37]; based on those studies, we expect 32,114 COPD patients (prevalence 8.18%). The control group will also come from a health-care area comprising 17 primary care centers, all of which pertain to the ICS (307,668 inhabitants over the age of 14 years; 32,248 patients).

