	**491.8 Other chronic bronchitis**	
	**496 Chronic airway obstruction, not elsewhere classified**	

ICD = International Classification of Diseases, with modifications approved by the World Health Organization

ICPC = International Classification of Primary Care (WONCA – World Organization of Family Doctors)

Additionally, a cohort will be selected in order to analyze the clinical and health-care variables. These patients must also meet the following additional inclusion criteria: 1) be able to perform spirometry; 2) meet spirometry criteria for a diagnosis of COPD: lung disease characterized by irreversible airflow limitation defined by a ratio of forced expiratory volume in 1 second [FEV_1_] to forced vital capacity ≤70% after a negative bronchodilator test, and in case of a positive postbronchodilator test (an increase in FEV_1 _of >12% and >200 mL after the use of 400 μg of salbutamol) not having a personal history of asthma, symptoms of atopy or a smoking habit of <40 pack-years. Additional exclusion criteria for this cohort were 1) a diagnosis of any terminal disease that indicates a survival prognosis <6 months, 4) advanced heart failure, 5) sequelae of pulmonary tuberculosis, and 6) lung cancer. All patients will have to give their written, informed consent to be enrolled.

Patients with other respiratory or nonrespiratory diseases can be included in the study provided they do not interfere with measurements. The testing of patients in a period of COPD exacerbation will generally be postponed until the disease has been stable for at least one month. Patients with exacerbated disease will not be excluded from the study, however; in case of continuously recurring exacerbations, the patient will be tested in that clinical state.

Calculation of the cohort size: For two-tailed comparisons, accepting an alpha risk of 0.05 and a beta risk of 0.2, to detect a statistically significant between-group CRQ score increment of 0.5 points (the minimum clinically significant difference) [38], and assuming a homogeneous standard deviation of 1.7 and a loss to follow-up of 10%, we have calculated that 220 patients will be required in each cohort. A simple random sampling procedure will be used to select the cohort patients.

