The implementation of the model rests on five types of action that have been undertaken in the preliminary phase. The first involves the formation of working groups and the identification at each primary care center of two referees, a physician and a nurse, who will be responsible for the program at that facility. Second, the physicians and nurses will attend informative sessions at the hospital and primary care center. These sessions will explain the clinical practice protocols and care pathways in the PROCESS management program. This action will also involve explaining the project to the health-care facilities' administrators and managers; official institutional approval and involvement will thereby be assured. The third will involve professional development and training through 1) a session in each primary care center, 2) training for a group of nurses, and 3) the preparation of patient educational support materials. The fourth set of activities will investigate the manner of performing spirometry at each primary care center. Based on the findings, the primary and tertiary care staffs will develop systems for calibrating equipment and assuring the quality of spirometries Training sessions will be set up to show primary care physicians and nurses how to perform and interpret spirometry. The fifth preliminary-phase action will be the introduction of a software application into the medical records of the primary health-care teams. This application will support clinical decision-making in accordance with the PROCESS protocols. This software is currently being developed by the ICS.

These five preparatory actions were begun in 2006. The preliminary phase is scheduled to be completed by the end of 2008, after which the clinical management program will be implemented in its entirety. None of the aforementioned actions will take place in the centers located in the control area of the city's health-care system. Nor will the clinical and organizational interventions be applied there. The care of COPD patients in the control area will continue according to the usual practices of physicians in those centers.

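### The CRQ test and the 220 per cohort treat patients as independent, although PROCESS is implemented through 17 primary care centers per area; 80% power is not assured and the test is too liberal if CRQ changes correlate within center.

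*Protocol article*

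**What the plan says.** All references are to the protocol article.

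- **Statistical analysis**, on the clinical dimension: "A test of comparison between two independent means will be used for comparisons with the control group". Multiple regression follows only if it proves necessary. Under Strengths and possible limitations of the study, regression is described as a way to adjust for differences between the groups. Correlation within center is not mentioned in either place.
- **Type of participant**, cohort size: "For two-tailed comparisons, accepting an alpha risk of 0.05 and a beta risk of 0.2", a between-group CRQ difference of 0.5 points, and "assuming a homogeneous standard deviation of 1.7 and a loss to follow-up of 10" per cent. The result is 220 per cohort, selected by simple random sampling. No ICC or design effect enters.
- **Setting**: "The study group will come from 17 primary care centers". The control area also has 17.
- **The COPD management model**: the preparatory work includes "the identification at each primary care center of two referees, a physician and a nurse", a training session in each center, and a review of how each center performs spirometry. Decision-support software goes into the primary care teams' records.
- **Discussion**: the results are expected to generalize at least to the Spanish national health-care system.
- **Table 2**: primary care clinic assignment is among the recorded variables.

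**The concern.** Patients of one center share clinicians, the two responsible staff, training and spirometry practice. The article gives reasons to expect uneven implementation. Ten of the intervention centers are run by the Catalan Health Institute and seven by other providers, the record systems differ, and the limitations section warns that consistent adherence at every facility will take great effort. Uneven uptake produces variation between centers in CRQ change, and taking pre-post differences does not remove it.

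A test of two independent means counts 198 patients per arm as 198 independent pieces of information. With positive within-center correlation there are effectively fewer, so the confidence interval is too narrow, the 5% test rejects too often, and the power is lower than stated. Quality of life is one of the two principal endpoints. The risk is an overconfident claim that the model works.

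**Working it through.** **Inputs from the article.** Two-sided alpha 0.05, power 80%, difference 0.5, SD 1.7, loss 10%, 220 per cohort (Type of participant); 17 centers per area (Setting). The article does not say whether 1.7 is the SD of the score or of the change; it is used here as the SD of the analysed quantity.

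**Assumed.** The ICC of that quantity, over the range 0.01 to 0.05; the same ICC in both areas; equal numbers of cohort patients per center.

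**Step 1: the plan's own figure.**
n = 2 × [1.7 × (1.960 + 0.842) / 0.5]² = 181.5, so 182 evaluable per arm. Dividing 181.5 by 0.9 gives 201.6, or 202; dividing the rounded 182 by 0.9 gives 203. The stated 220 is about 8% above this (220/203 = 1.08) and does not follow from the inputs. The discrepancy is in the conservative direction.

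**Step 2: power as planned, patients independent.**
Evaluable: 220 × 0.9 = 198 per arm. SE = 1.7 × √(2/198) = 0.171, and 0.5/0.171 = 2.93. Power is 83.3% by normal approximation.

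**Step 3: allow for center.**
Patients per center: m = 198/17 = 11.65. Design effect: DE = 1 + (m − 1) × ICC. Effective n = 198/DE. SE = 1.7 × √(2 × DE/198). Power is taken from the normal approximation and from a noncentral t with 34 − 2 = 32 df. The true error of the unadjusted 5% test is 2 × [1 − Φ(1.96/√DE)].

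| ICC (assumed) | DE | Effective n per arm | Power, normal | Power, t on 32 df | True type I error, unadjusted test |
|---|---|---|---|---|---|
| 0 | 1.00 | 198 | 83.3% | 81.0% | 5.0% |
| 0.01 | 1.11 | 179 | 79.4% | 77.0% | 6.2% |
| 0.02 | 1.21 | 163 | 75.7% | 73.1% | 7.5% |
| 0.05 | 1.53 | 129 | 65.7% | 63.0% | 11.3% |

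**Step 4: what the surplus in 220 covers.**
By normal approximation, 80% power holds while DE ≤ 198/181.5 = 1.091, which is ICC ≤ 0.091/10.65 = 0.0086. On 32 df the limit is about 0.0024. The surplus is therefore not a usable allowance for clustering.

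**The case against.** **Simple random sampling makes the independent test valid.** This stands for a description of these two particular areas. It does not stand for the question the article asks, which is whether the model is effective and would be elsewhere. For that question, variation between centers is part of the error.

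**The ICC is assumed and the loss may be small.** This stands. No ICC is given, and at 0.01 or below the effect is modest. Stable center differences cancel in a pre-post change, so the relevant ICC is that of the change and may be lower than that of the score. Also, program uptake cannot vary among control centers, which receive none of it. If correlation existed only in the intervention area, the average design effect would be 1 + (m − 1) × ICC/2, so an ICC of 0.02 in that arm alone would act like 0.01 in both.

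**Details of variance estimation belong in a fuller document.** This would answer mere silence. Here the article positively names the test and the inputs of the calculation, and both assume independence.

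**A stronger reading: the admissions endpoint suffers most, with grossly inflated error.** A reader might infer this from the large number of patients per center. The text does not support it. Indirect standardization is named first, and regression follows only if possible, with no unit of analysis stated. The outcome is a change in annual rate, so a cross-sectional design effect overstates the inflation. Nor does it help to argue that the same patients contribute to both periods. The variance of a within-patient difference is 2σ²(1 − ρ), so ignoring a positive ρ makes the standard error too large, not too small.

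**Adjusting for center cannot rescue a design with one area per arm.** This is correct as a limit on the remedy. It is no reason to leave the center-level error out.

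**Conclusion.** The point holds for the CRQ endpoint. As written, the test is too liberal whenever CRQ change correlates positively within center, and 80% power is not assured. At assumed ICCs of 0.01 to 0.05, power on 32 df falls from about 77% to 63% (79% to 66% by normal approximation), and the nominal 5% test has a true error of about 6% to 11%. The direction needs only a positive ICC; the size depends on the assumed ICC, its equality across areas and equal center sizes. The 220 per cohort also fails to reproduce from its own inputs, which need about 202 to 203.

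For admissions, only a conditional version holds: if the regression uses patient-level records, the pre-post change needs the same allowance for center. No size is claimed for that endpoint.

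**What to change.** 1. Replace the independent-means test with a comparison of CRQ change that accounts for primary care center. Use either a random center effect, or cluster-robust standard errors with a small-sample correction and about 32 df for the 34 centers.
2. Restate the power of the existing cohort over an explicit ICC range, without enrolling more, and say whether the SD of 1.7 refers to the score or to the change.
3. Reconcile 220 with the stated inputs, or name the allowance that accounts for the difference.
4. If the admissions regression uses patient-level records, apply the same center-level adjustment to the pre-post change.
5. State as a limitation that, with one non-randomized area per arm, adjusting for center does not remove area-level confounding.

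The cost is in wording and analysis only, because clinic assignment is already collected (Table 2). The downside is wider intervals and a less favourable stated power.
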